### **Strategies for ongoing engagement of key stakeholders**

This study has been designed to support ongoing engagement of key stakeholders and scalability. The leading role of the DPHO for Kathmandu District as a key decision maker within the government health sector and the experience of HERD in engaging with MoHP to influence decisions mean that scaling up the approach across the country is viable. The HR Strategy is still in its infancy, evidence of how to practically address the objectives of the strategy is urgently needed in order for the strategy to have an impact nationally. This study, and its strong connections with District health structures and MoHP has the potential to have an important and timely impact on policy; and will feed into the design of the 3rd National Health Sector Programme.

There will be continual engagement with MoHP and key practitioners throughout the life of the project through the following strategies:

- Steering Group meetings (as detailed in section 2.8.1) will be held every 3 months and will include active participation of key decision makers within the government health sector
- Participation of key policy makers and practitioners within the methodological design of the implementation research project (for example in the initial intervention design workshop, the midpoint national workshop and the reflective and interactive workshops)
- Participation and sharing of project process and outcomes within regional and national health reviews, which are attended by all DHOs, regional directorate and senior officials from the ministry of health
- Participation in Joint Annual Review (JAR) - a high level fora which brings together the ministry and external development partners
- The research team constitutes academia, local researchers, policy makers and implementers which help ensuring strategic engagement of relevant stakeholders
- Proposal focus fits within national priority area, is of interest to key stakeholders and will feed into ongoing discussion and debates in NHSP 2 and development of NHSP 3
- Proposal builds directly on the success and innovation taken forward by a DHO, and there is a core interest group of DHOs (implementation districts) who will be engaged throughout the process
- The proposal has a number of approaches designed to foster engagement of stakeholders throughout i.e national, regional and district level workshops, meetings, dissemination meetings

## Data quality assurance/ management

*Quantitative Data Collection:* The motivation questionnaire will be conducted by enumerators trained to collect the data correctly. A supervisor will check all questionnaires for quality. As the questionnaire is a straightforward list of 10 questions on a scale of 1 to 5, it is not envisaged to cause major data collection issues. However, questionnaires will be checked throughout the process of data collection to ensure that they are complete and filled correctly. All quantitative data will be double entered into CsPRO. Checks will be run to identify missing data and any anomalies. Data will be exported to STATA to carry out the quantitative analysis. All questionnaires will have a unique identifier which will not only ensure complete anonymisation of the data, but will also enable good data management and the ability to go back to original questionnaires to check any inconsistencies or incomplete data.

*Routine Data***:** Routine data will be collected from HMIS reports at district level and verified at the sampled health facilities. This will give an indication of the completeness and accuracy of the data. Any anomalies can be raised with the health facilities.

*Qualitative Data:* HERD’s researchers are well trained and experienced in the use of qualitative methods, including interviews, focus group discussions and observation. Interviews and focus group discussions will be recorded using digital recorders and written up as soon as soon they take place wherever possible. The researchers will also keep a reflective diary which can be used to inform the analysis and to understand why certain methodological decisions have been taken. The use of several members of the team to develop the coding framework and reflect on the analysis will provide inter-rater reliability of the qualitative findings.

#

# Gender considerations

Health staff within the districts are both female and male and will benefit from the HWSP. We will understand the specific concerns of different cadres of female and male staff during the Doti evaluation and the contextual analysis of the intervention districts and ensure the refined HWSP responds to these needs. For example, nurses in Nepal are all female and often find it difficult to remain in remote areas and we address these concerns where appropriate in the HWSP.^7^ Each district also has 700 female community health volunteers, who should benefit from the intervention through enhanced supervision processes.

There is a clear need to improve health outcomes in Nepal, particularly in areas of sexual, reproductive and maternal health. Given the Doti experience we anticipate that the HWPM may impact positively on the ability of poor women, men, boys and girls to access quality health services.

The HWSP includes a process of developing and refining job aides, and this will include a focus on processes, for example ensuring greater support to women and particularly marginalised communities. As part of the process evaluation we will track service delivery indicators by gender, caste and ethnicity, and identify gaps and respond accordingly.

We will do our utmost to ensure that both female and male staff benefit from the HWSP and are able to participate in research processes to evaluate its impact. As detailed in our methods within the health sector and at the community level we will capture male and female perspectives and also ensure representation by age, class, caste and ethnicity. The team will do their utmost to ensure that interviews and data collection is done at a time and a place that is convenient for participants.

The core team has 4 men and 3 women. There are 4 men ([name], [name], [name] and [name]) and 3 women ([name], [name] and [name]). The core team and their roles and responsibilities are outlined in section 2.8.1. All team members are committed to promoting gender equity throughout the research process.

#

# Ethical issues

The study team will work closely with District Authorities and community leaders to ensure that all stakeholders are well informed of the study and its purpose. The study will be reviewed by Ethical Review Committee of WHO, it will also seek ethical approval from the Liverpool School of Tropical Medicine and from Nepal Health Research Council (NHRC).

*Potential Issues:* health workers may feel unable to refuse participation or able to speak freely for fear of reprisals from senior managers. To address these issues during recruitment research staff will explain clearly that all data provided whether by questionnaire (motivation tool) or during qualitative interviews will remain anonymous. We will be careful in the characterisations used to locate quotations, for example not naming Districts directly (referring to Hill district or Terai District, rather than by name) in order to maintain confidentiality during reporting and dissemination.

All participants, whether they are health workers, district officials or community members will be given sufficient information about the study and be provided with opportunity to ask any questions and think over participation on their own before giving consent.

*Recruitment for Interviews with staff and HFMC members:* The research team will visit each of the randomly selected health facilities (as above) and present to all staff and to HFMC members: the study, its purpose and inclusion criteria for both the questionnaire and the qualitative elements. They will then leave information sheets and consent for all staff to read, allowing at least 24 hrs to consider their participation or not. They will make a time with the health facility to return to conduct the motivation questionnaire and qualitative interviews. At these start of these interviews the participants will be encouraged to ask any questions about the study. If they are still willing to participate, they will then fill in their consent form.

The researcher will be well trained to explain the study and the HWs right not to be involved should they wish so or leave the interview at any point of time. Qualitative interviews will be conducted at a private location away from the health facility to ensure confidentiality.

*Recruitment of community members:* If community members from the groups identified above are potentially interested in the study, the researchers will talk through the information sheet and consent process. If the potential participant is still interested in being part of the focus group, the researchers will let them know the time and the venue. At the start of the focus group the researchers will again go through the information sheet and take informed consent from the participants, including consent to record the FGD.

*Maintaining Confidentiality and Storage of Data:* All transcripts and questionnaires will be anonymised. The identity of the participants will not be known to others apart from the research team. The researcher will write the unique identifier on the consent form, once consent has been given and this unique identifier will then be used on all collected data. The consent forms will be kept in a locked drawer in HERD’s office which is locked and has a security guard. All data and analysis on HERD’s computers will be under a password protected system.

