# Detailed description of the project

**Background information and rationale**

A well-performing workforce is described by WHO as one in which staff are available, competent, responsive and productive.^3^ Several studies have identified limitations within Nepal’s health workforce in all of these aspects. For example, health facility surveys have shown that only 64-80% of doctors, 68-81% of nurses and 81-92% of paramedics are available for work.^4^ These Human Resource (HR) problems have a direct impact on health service delivery, particularly maternal and new born services, e.g. the lack of staff to support safe delivery in government facilities was not due to the lack of trained staff but the inability to attract and retain them.^5^ The impact of supervision has also been assessed in a sample of districts and only found to have a minimal impact on health service delivery,^6^ hence lack of supportive supervision continues to be an issue. Recent capacity assessments of the health sector workforce have identified the need to strengthen leadership and management.^7^ Studies have found that HR issues – recruitment, deployment, retention and motivation – are very much context specific and vary within mountain, hill and Terai (plains) districts. A further limitation in the development of leaders is highlighted by the observation of the “drifting away of senior female staff across the health sector”.^8^ The lack of opportunities for career progression affects women across Nepal’s health sector and serves to de-motivate female staff.

Practical experience aligns with these studies, the Director of National Health Training Centre (collaborator on this study) who developed the pilot in Doti, and other DPHOs have identified the following issues from workforce assessments and from the direct experience:

- High turn-over and poor retention of staff.
- Lack of job descriptions, and when they do exist, they tend to be based on tasks rather than overall outcomes.
- Limited supervision, particularly supportive supervision that is effective in improving health workforce performance hence health outcomes.
- Lack of context specific action planning to resolve HR performance problems when identified
- Lack of accountability to communities.

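### Staff are promised anonymous data, but one identifier links consent form to data, and access to identities is not limited by role

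*Protocol*

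**What the plan says.** Under Ethical issues, the protocol names one participant risk: "health workers may feel unable to refuse participation or able to speak freely for fear of reprisals from senior managers". Its first answer is what research staff will explain at recruitment, namely that "all data provided whether by questionnaire (motivation tool) or during qualitative interviews will remain anonymous". The data quality section repeats the idea: "All questionnaires will have a unique identifier which will not only ensure complete anonymisation of the data".

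The confidentiality paragraph of the same ethics section then sets the working rules. On access: "The identity of the participants will not be known to others apart from the research team". On the identifier: "The researcher will write the unique identifier on the consent form, once consent has been given", after which that identifier is carried on everything collected from the person.

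The section on engaging stakeholders describes who is on the team: "The research team constitutes academia, local researchers, policy makers and implementers which help ensuring strategic engagement of relevant stakeholders". It also gives a leading role to the district public health officer for Kathmandu. The background mentions "the Director of National Health Training Centre (collaborator on this study) who developed the pilot in Doti".

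Other controls are stated. Consent forms are kept under lock in the research organisation's guarded office, computers are password protected, qualitative interviews are held in private off the facility's premises, staff have at least 24 hours to decide, and quotations will not name the district.

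**The concern.** The promise of anonymity is meant to secure free consent and candid answers from employees who may feel exposed. If it is not true, staff agree on a wrong understanding of what could be traced to them. They are asked about their motivation, their supervision and how well a model backed by the district office works.

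The second difficulty is the boundary. If the research team is as wide as the stakeholder section says, the access rule does not by its own terms keep health-service officials away from participants' identities. The protocol itself treats confidentiality as a validity issue: Step 4 rules out following individuals because confidentiality worries could undermine the answers.

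**Working it through.** No figure in the protocol is in dispute, so the check sets the statements side by side.

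1. **Is the data set anonymous?** Recruitment promise: anonymous. Data quality section: completely anonymised by the identifier. Confidentiality paragraph: the research team knows who the participants are, and the same identifier is on the consent form and on the data. Anyone holding both can match answers to a person. Such data are coded. The first two statements and the third cannot all be true.

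2. **Is the link needed?** The answer differs by part of the study.
   - *Doti pilot:* questionnaire scores are used to choose staff for interview and are then compared with what they say. A link between the two is needed.
   - *Three-district baseline and endline questionnaires:* Step 4 says individuals will not be followed, and the sample size section describes a different random sample after the intervention. The data quality section wants an identifier so that queries can be traced to the original questionnaire; a number on the questionnaire does that without appearing on the consent form. No use for the consent-form link is stated here. One entry in the summary table of methods, under Objective 3, does speak of following up baseline health workers. I take Step 4 and the sample size section as governing.

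3. **Who may know identities?** The access rule stops at the research team and gives no roles. The stakeholder section's description of the team includes policy makers and implementers. No sentence in the confidentiality paragraph excludes them.

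4. **What do the other controls do?** Locks and passwords keep outsiders away from forms and files. Off-site interviews protect the setting, and unnamed districts protect published quotations. None of them says which team members may open the drawer or the files.

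5. **How many people does the wording reach?** Questionnaires: 65 in Doti plus 280 invited at each of two rounds, 65 + 280 + 280 = 625. With the 250 analysable per round that the protocol expects after refusals, 65 + 250 + 250 = 565. These are questionnaires, not distinct people, since a worker could be drawn in both rounds. Staff interviewees come under the same promise, including about ten in Doti.

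**The case against.** The best reply is that the protection in practice is better than the wording. The consent forms, the only stated link, are locked in the research organisation's office. In the ethics section the research team reads as the field team that visits facilities and returns to interview. Elsewhere enumerators administer the questionnaire and two of the organisation's researchers read the transcripts. The wide description of the team comes from a passage about engagement, not data access. Team roles are referred to a section 2.8.1 that is not in the document at hand, and consent pages were removed, so a limit on access may be stated there. A study number on a consent form is also ordinary practice.

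Much of this stands, and it rules out three stronger readings that a reader might infer.

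- *That the reprisal risk is uncontrolled.* It is not; several controls are stated.
- *That respondents' own managers sit on the team.* The documents do not show this. The officer with the leading role serves Kathmandu, which is neither Doti nor one of the three intervention districts. The model's developer has left the Doti post and is called a collaborator. Implementers are not defined, and Step 2 lists the research team separately from district stakeholders. Doti is the nearest case, because staff interviewees must have worked there for the last five years and many probably served under the developer. Present authority over them is not shown.
- *That the results are biased towards the model.* This is possible but not demonstrated. Effectiveness is judged by the change from baseline to endline, so favourable answering of equal size at both rounds would cancel. The Doti questionnaires serve to choose a tool, not to estimate an effect.

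The reply does not repair the contradiction between the promise and the identifier rule, or supply the missing role limit in the paragraph where access is defined.

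**Conclusion.** The point holds in a limited form. As written, the assurance given to staff is untrue: the data are confidential and coded, not anonymous. The access rule sets no limit by role although the team is said to include policy makers and implementers. The named reprisal risk is therefore not adequately controlled, despite the partial controls. This is a matter of participant protection and truthful consent; no numerical effect on the results is claimed. It should be corrected.

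The conclusion on access assumes that research team means the same in the ethics section as in the stakeholder section, and that section 2.8.1 sets no narrower limit. If it does, that part reduces to a cross-reference. The conclusion on anonymity rests on neither assumption.

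**What to change.** 1. **Correct the promise.** In Ethical issues, the data quality section and the staff information, wherever a link is kept, replace the claims of anonymity and complete anonymisation with: *confidential, identified only by a code*. This includes Doti, where the link has a purpose.

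2. **Limit access by role.** In the confidentiality paragraph, replace the reference to the research team as a whole. Only field researchers and data staff who hold no health-service post should hold the consent forms, the identifier link and identifiable recordings. Other team members see de-identified material only, which may include anonymised transcripts.

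3. **Remove the link where it has no use.** For the baseline and endline motivation questionnaires in the three districts, keep the questionnaire number off the consent form and file consents separately. A worker who also gives an interview needs a separate number for the questionnaire. Align the Objective 3 entry in the methods table with Step 4, since this step depends on individuals not being followed.

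The cost is wording and a short access list. No sample, outcome or analysis changes. The one small loss is that a three-district questionnaire could not later be withdrawn by name, which the staff information should say.
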